### Quality of life

The quality of life of patients will be assessed by using EuroQol. EuroQol is a generic measure of the respondents’ health-related quality of life and utility values [26, 27]. The questionnaire consists of five items covering the areas of mobility, self-care, usual activities, pain/discomfort, and anxiety/depression (EQ-5D). Each item has three levels: no problems, some problems, or extreme problems. The EQ-5D scores are converted to a single index value (ranging from 0 for the worst health state to 1 for the best health state) [27]. A higher score represents a higher quality of life. The reliability and validity of the Japanese version have been established [28], and used in patients with diabetes in Japan [29].

### Attitude of physicians toward depression

Attitudes of physicians toward depression will be measured by using the Depression Attitude Questionnaire (DAQ) [30]. This questionnaire consists of 20 items based on three themes: the conceptual model of the responder, the respondents’ value judgments, and their practical response. Answers are marked on a 100-mm visual analogue scale ranging from “strongly disagree” (0 mm) to “strongly agree” (100 mm). The DAQ has been translated into Japanese, and its reliability and validity have been verified [31]. Receiving completed DAQ will be regarded as the physicians agree to participate in the questionnaire survey.

### Sample-size calculations

We calculated sample size as 550 patients (165 for the depression group and 385 for the non-depression group) having (1) a 30 % prevalence of depression, (2) 10 % difference in microalbuminuria rate (18 % in the depression group and 8 % in the non-depression group), and (3) an 88 % chance of detecting a true difference in microalbuminuria at the 5 % level of significance. Calculation was based on the chi-square test with continuity correction and we did not take into account of adherence since it might be an intermediate variable. The prevalence of depression in patients with diabetes was 20 % in previous studies [5, 6, 10, 11]; however, we estimated 30 % owing to the inclusion of patients from psychiatric clinics in our study. The prevalence of microalbuminuria was estimated by using the data of the Japanese Society of Nephrology [18] and those from a previous study [11].

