**Methods/Design:**

In this multicenter cohort study, 550 patients with type 2 diabetes aged 20 years and older will be recruited at 20 outpatient clinics in general medicine and psychiatry. We will measure depression (Patient Health Questionnaire), medication adherence (medication possession ratio, Morisky Medication Adherence Scale, and one-item hypoglycemic medication adherence scale), and renal function (urinary albumin-creatinine ratio and estimated glomerular filtration rate) at baseline and at the 12-month follow-up. The primary endpoint is decline of renal function at 12 months. The secondary endpoints include clinical variables, quality of life, and the attitude of professionals toward depression. We will perform multivariable linear regression analysis to evaluate the effects of medication adherence on the decline of renal function in comorbid patients with type 2 diabetes and depression.

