### Participants

All patients who meet inclusion criteria during the study period will be invited to participate in the study. Participants will be eligible for the study if they (1) are 20 years and older, (2) outpatients with type 2 diabetes receiving hypoglycemic medications, and (3) can complete a questionnaire in Japanese. Patients will be excluded if they (1) have cognitive impairment, (2) are pregnant, and (3) have severe disease of the adrenal glands, liver dysfunction, or severe renal impairment (serum creatinine ≥ 2.0 mg/dL).

Eligible patients will be approached by physicians at each site. After an explanation of the study, written informed consent will be obtained from each patient. Patients will be able to access research staff members who are not in charge of their treatment to withdraw from the study at any time.

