### Study endpoints

The primary outcome is the decline of renal function in four subtypes categorized according to depression and adherence (depression/adherence: +/−, +/+, −/+, −/−) at 12 months. The secondary outcomes include clinical variables, quality of life, and attitude of physicians toward depression. We assess physician attitudes to depression to confirm no effects of the attitudes on primary outcome in a sensitivity analysis. Previous systematic review suggests necessity for cohort studies to examine information on patients with multimorbidity across all ages and socioeconomic groups [16]. Although analyses of secondary outcomes will be underpowered, we include the analyses in the protocol for confirmation of the analysis of primary outcome and implication for the future studies.

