### Data analysis

We will use multivariable linear regression analysis to evaluate the effects of medication adherence of comorbid patients with type 2 diabetes and depression on the decline of renal function. We will consider other potential confounding factors including smoking, hypertension, hyperlipidemia, and HbA1c. The risk of decline of renal function will be estimated for four groups by adherence (+/−) and depression (+/−) by odds ratio and 95 % confidence interval.

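### The 88% power belongs to the overall depression contrast on all 550 patients, not to the four-group depression-by-adherence comparison named as primary, and the analysis section does not name the powered contrast

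*Protocol article*

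**What the plan says.** All references are to the protocol article.

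- **Sample-size calculations:** "We calculated sample size as 550 patients (165 for the depression group and 385 for the non-depression group"). The rates are 18% and 8% for microalbuminuria, with 88% power at the 5% level by a continuity-corrected chi-square test. On adherence: "we did not take into account of adherence since it might be an intermediate variable".
- **Study endpoints:** "The primary outcome is the decline of renal function in four subtypes categorized according to depression and adherence", assessed at 12 months. The same section says that the secondary outcomes will lack power. It gives no such warning for the primary outcome.
- **Data analysis:** a linear regression for the adherence effect in patients with both conditions, and then "The risk of decline of renal function will be estimated for four groups by adherence" and depression, as odds ratios with 95% confidence intervals. No comparison of all depressed with all non-depressed patients is named.
- **Background:** aim 1 is whether depression predicts loss of renal function. Aim 2 is how adherence relates to depression and to that loss.
- **Abstract, Methods/Design:** "550 patients with type 2 diabetes aged 20 years and older will be recruited at 20 outpatient clinics". The number recruited equals the number calculated. Under Participants, patients may "withdraw from the study at any time".

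**The concern.** The sample size, the primary outcome and the analysis do not address the same comparison. Treating adherence as a possible intermediate is a sound reason to leave it out of an overall depression contrast. It gives no support to a power figure for an outcome that is itself split by adherence. Because the warning about low power is limited to the secondary outcomes, a reader may take the four-group primary comparison to be adequately powered. The one contrast that was sized is not listed among the analyses.

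At stake is how a null or imprecise four-group result is read. The Discussion intends the depressed, poorly adherent group to guide screening and intervention, so the precision available for that group should be stated plainly.

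**Working it through.** **Inputs from the article.** n₁ = 165, n₂ = 385, k = 385/165 = 2.333, p₁ = 0.18, p₂ = 0.08, d = 0.10, 5% level, continuity correction. The article does not say whether the test is two-sided; a two-sided test reproduces its figure.

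**Inputs assumed, because the article gives none.** Low adherence in 20% to 40% of patients; a 10-point difference in risk between adherence groups; loss of 10% or 20% over 12 months.

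**Step 1. Reproduce the 88%.**
- Effective size after the continuity correction: n′ = [n₁ − (1 + 1/k)/(2d)]²/n₁ = (165 − 1.4286/0.20)²/165 = 157.86²/165 = 151.0.
- Pooled risk: (165 × 0.18 + 385 × 0.08)/550 = 60.5/550 = 0.11.
- z = [d√n′ − 1.96√(0.11 × 0.89 × 1.4286)] / √(0.18 × 0.82 + 0.08 × 0.92/2.333) = (1.229 − 0.733)/0.423 = 1.17.
- Power = Φ(1.17) = 87.9%. Exact enumeration of the corrected test gives 88.6%.

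The stated figure is right, and it uses all 550 patients.

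**Step 2. Apply loss to the same contrast.**

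| Assumed loss | Analysed | Formula | Exact |
|---|---|---|---|
| 0% | 165 + 385 | 87.9% | 88.6% |
| 10% | 148 + 346 | 84.3% | 85.1% |
| 20% | 132 + 308 | 79.8% | 80.7% |

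**Step 3. Adherence effect within the depressed group.** This is the comparison in the first sentence of the Data analysis section, and one of the contrasts inside the four-group outcome. Hold the depressed average at 18%. With a low-adherence share w and a 10-point difference, the risk in adherent patients is 0.18 − 0.10w, and the risk in low-adherence patients is 0.10 higher.

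| Low adherence | Split of 165 | Risks | Exact corrected power |
|---|---|---|---|
| 20% | 33 / 132 | 26% vs 16% | 21% |
| 40% | 66 / 99 | 24% vs 14% | 31% |

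Without the continuity correction these become 28% and 38%. For 88% power with the correction, the difference would have to be about 27 points (20% low adherence) or 20 points (40%).

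**Step 4. Can the four groups return the overall depression effect?** Yes, in unadjusted form. Risk in the depressed = w × risk(depressed, low adherence) + (1 − w) × risk(depressed, adherent), with w the observed low-adherence share in that group, and likewise for the non-depressed. The odds ratios themselves compare individual groups. A depression contrast read at a fixed adherence level conditions on the possible intermediate, so it is not the effect that was sized.

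**The case against.** Three objections have force.

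**The depression effect is recoverable.** A reader might infer that the four-group analysis cannot answer aim 1. The article does not support that: Step 4 shows that the four unadjusted risks recombine into the overall contrast, and adherence is described only as something that might be intermediate. A one-paragraph analysis section may also leave the pooled contrast to a fuller plan that is not shown. What stands is narrower. The contrast that justifies the sample size is not named where the analyses are listed.

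**Not every four-group contrast is weak.** A reader might infer that all of them have low power. Under the risks in Step 3, depressed/low-adherence against non-depressed/adherent, with the comparator kept at 8%, has about 77% power (33 vs 308, 26% vs 8%) or 88% (66 vs 231, 24% vs 8%). Lower figures for this contrast arise if the low-adherence cell is kept at the depressed average of 18%, but that contradicts a 10-point adherence effect. The shortfall shown here is for the adherence comparison within depression.

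**The 88% is openly tied to two groups, and the four-group results are already estimates with intervals.** Both statements are true, and they limit the harm. They do not remove the conflict with a primary outcome defined by four groups, or with a power warning confined to the secondary outcomes.

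**Conclusion.** The concern holds in this limited form: the 88% is correct for depression against no depression with all 550 patients analysed, and it does not apply to the primary comparison as the article defines it. The mismatch itself rests on the text alone. Its size rests on assumptions: with 20% to 40% low adherence and a 10-point difference around an 18% average, power within the depressed group is about 21% to 31%. These figures keep the microalbuminuria rates used in the article's own calculation.

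The lack of an allowance for loss is minor. Even at an assumed 20% loss the two-group contrast keeps about 80–81% power, and the article gives no expected loss rate.

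**What to change.** 1. In Data analysis, name the overall comparison of depressed with non-depressed patients, without adherence in the model, as the powered analysis for aim 1.
2. In Study endpoints and Sample-size calculations, state that the 88% covers only that contrast with 550 analysable patients. Add the power under loss: about 84–85% at 10% and about 80–81% at 20%, with the rates labelled as assumptions.
3. In the same two sections, state that the four-group comparison was not sized and is reported as odds ratios with 95% confidence intervals.

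The four-group outcome need not be demoted, since adherence in patients with both conditions is the study's declared focus, and no mediation analysis is required to cure this point. The cost is amendment wording, one extra model and a less favourable power statement. No additional patients are needed.

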## Background

Prevention, or slowing the progression, of diabetic nephropathy is one of the important goals in diabetes care [1, 2]. As the kidney disease progresses, end-stage renal disease (ESRD) occurs and requires either dialysis or transplantation, which places significant burden on the patient and the society. Diabetes is one of the predictors of a poor perceived quality of life in patients with ESRD [3], and the prevalence of diabetes could impose an increasing economic burden due to substantial costs for patients with ESRD [4].

Depression is observed in approximately 20 % of patients with diabetes [5, 6]. Although adherence to hypoglycemic medication is important for the prevention and management of diabetic nephropathy [2], a meta-analysis indicates that depression is associated with lower adherence to hypoglycemic medication in patients with diabetes [7]. Furthermore, depression also adversely affects adherence to other key medications for hypertension and hyperlipidemia - the main risk factors of diabetic nephropathy [8]. Considering the high prevalence of depression and that depression is rather commonly undiagnosed in patients with diabetes [9], the impact of depression on diabetic nephropathy is a growing concern.

The literature has reported the morbidity and mortality of kidney disease in patients with depression. A recent meta-analysis showed that depression was observed in 21.4 % of patients in chronic kidney disease (CKD) stage 1–5 [10]. Comorbid patients with diabetes and depression had higher risks of microalbuminuria [11] and ESRD than those without depression [12]. Patients with diabetic nephropathy who have had a depressive episode were more likely undergo dialysis than those without a depressive episode [13], and the mortality was 1.5-fold higher in diabetes patients with depression than in those without depression [14, 15].

In patients with type 2 diabetes, we aim to examine (1) depression as a predictor of renal function decline, and (2) how adherence to hypoglycemic medication relates to depression and renal function decline.

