### Data collection

Data will be collected at routine clinic visits by coordinating staff at baseline and 12 months. The data include patients’ demographic variables (e.g., age, gender, and smoking status), body mass index, prescription, blood pressure, laboratory data (e.g., glucose level, HbA1c, total cholesterol, low- or high-density lipoprotein cholesterol, triglycerides, serum creatinine, and urinary albumin-creatinine ratio [ACR]), and diabetic complications. Table 1 shows the primary measures and timings for measurement.

**Table 1 Tab1:** Measures and timings for measurements

	Scale	Baseline	1 Year
Renal function	urinary albumin-creatinine ratio (ACR) estimated glomerular filtration rate (eGFR)	●	●
Depression	Patient Health Questionnaire (9-item): PHQ-9	●	●
Adherence	Medication Possession Ratio (MPR) Morisky Medication Adherence Scale (MMAS-8) Oral Hypoglycemic Agent (OHA) adherence	●	●
Quality of life	EuroQol	●	●

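### Adherence is named a possible intermediate, yet the stated analyses give no depression contrast free of adherence and no model for the depression–adherence link

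*Protocol article*

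**What the plan says.** **Aims.** The Background section of the protocol article sets two aims: whether depression predicts loss of renal function, and "how adherence to hypoglycemic medication relates to depression and renal function decline". The same section reports that depression goes with lower adherence and that adherence matters for preventing nephropathy.

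**Sample size.** The Sample-size calculations section compares depressed with non-depressed patients (165 and 385; 18% and 8% with microalbuminuria). It explains the absence of adherence thus: "we did not take into account of adherence since it might be an intermediate variable".

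**Primary outcome.** The Study endpoints section fixes it as "decline of renal function in four subtypes categorized according to depression and adherence".

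**Analysis.** The Data analysis section states two analyses. One begins "We will use multivariable linear regression analysis to evaluate the effects of medication adherence of comorbid patients with type 2 diabetes and depression". In the other, risk is "estimated for four groups by adherence (+/−) and depression (+/−) by odds ratio and 95 % confidence interval". The adjustment set is "potential confounding factors including smoking, hypertension, hyperlipidemia, and HbA1c".

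**Timing.** "Data will be collected at routine clinic visits by coordinating staff at baseline and 12 months". The Medication adherence section defines low adherence as a medication possession ratio (MPR) below 80%, with the MPR counted over 365 days.

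**The concern.** The article gives adherence two roles. In the sample-size section it is a step that may lie between depression and the kidney, so the contrast that is powered ignores it. In the endpoint and analysis sections it is a second exposure that, with depression, defines the groups being compared. Both roles are legitimate, but they answer different questions, and only the second has a stated analysis.

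Two things follow. The contrast that the study is sized for, which is also the natural answer to aim 1, is not among the stated analyses. And although aim 2 names the relation of adherence to depression, no stated analysis has adherence as its outcome. If adherence does mediate, a depression effect read within adherence levels would be taken as the effect of depression when it is only the part that bypasses adherence.

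**Working it through.** **1. The plan's own figure.** Inputs from the Sample-size calculations section: 18% vs 8%, allocation 165:385, 5% level (taken as two-sided), chi-square with continuity correction, 88% power. The formula gives 166 in the depression group, so 166 × 550/165 ≈ 553 in total, against 165 and 550 stated. Power at 165/385 is 87.9% by the corrected normal formula and 88.6% by exact enumeration. The figure reproduces. It covers only the overall depression contrast.

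**2. Aims against stated analyses.**

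| Question | Stated analysis |
|---|---|
| Aim 1: depression and renal decline, overall | None; this is the contrast that was sized |
| Aim 2: adherence and renal decline | Linear regression in comorbid patients; four-group odds ratios |
| Aim 2: depression and adherence | None with adherence as outcome |
| Joint risk by depression and adherence | Four-group odds ratios |

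If the linear regression were fitted to the whole cohort with a depression term beside adherence, that term too would be conditional on adherence.

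**3. How much a within-adherence contrast can leave out.** The article gives no adherence frequencies and no adherence effect, so the inputs here are assumptions. Let a0 and a1 be the share with low adherence in non-depressed and depressed patients, and d the risk added by low adherence, the same in both. Then

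- 0.08 = r0 + a0·d and 0.18 = r1 + a1·d, where r0 and r1 are the risks among adherent patients;
- part through adherence = (a1 − a0)·d; remaining part = r1 − r0.

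Take a0 = 0.20, a1 = 0.40, d = 0.15:

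- r0 = 0.08 − 0.03 = 0.05 and r1 = 0.18 − 0.06 = 0.12.
- Cell risks: non-depressed 5% (adherent) and 20% (low); depressed 12% and 27%.
- Odds ratios against the first cell: 1, 4.75, 2.59, 7.03.
- Through adherence: 0.20 × 0.15 = 0.03, or 3 of the 10 points. Within either adherence level the depression difference is 7 points.

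The odds-ratio scale hides this. The overall odds ratio is (0.18/0.82)/(0.08/0.92) = 2.52. Within levels it is 2.59 among adherent patients and 7.03/4.75 = 1.48 among the others. Neither shows the 3 points, so a risk difference is the better scale.

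**4. Range.** With a0 of 20–30%, a1 of 30–50% and d of 5–20 points, the share is (a1 − a0)·d/0.10. It is 0 at 30% vs 30%, and 0.30 × 0.20/0.10 = 60% at 20% vs 50% with 20 points.

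**5. Cell risks alone do not settle it.** Hold assumed cell risks at 22% and 15% (depressed, low and adherent) and 11% and 7% (non-depressed), with a0 = 30%. For a1 of 30%, 45% and 60% the overall difference is 8.9, 9.95 and 11.0 points. The part through adherence is (a1 − 0.30) × 0.07 = 0, 1.05 and 2.1 points, that is 0%, about 11% and about 19%. The four odds ratios are the same in all three cases.

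**6. Is the missing link estimable?** With 165 and 385 patients, the uncorrected chi-square has about 71% power for 30% vs 20% low adherence and about 96% for 35% vs 20%. The indirect effect is less certain: an approximate product-of-coefficients calculation gives 28% power at 40% vs 30% with a 5-point effect, and over 99% at 60% vs 30% with a 20-point effect.

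**The case against.** **Aim 2 is worded as a relation.** It promises no mediated share, and the Discussion says that the results should help to identify a high-risk group with depression and poor adherence. A four-group table serves that purpose directly. This stands: a reader might infer that the study undertook to measure how much of depression's effect runs through adherence and then failed to plan for it, but the article does not support that.

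**The cross-classification is not the only stated analysis, and not every contrast in it holds adherence fixed.** This also stands. The adherence regression is stated too, and comparing depressed low-adherence patients with non-depressed adherent ones changes both factors.

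**Group sizes give the crude answers.** Counts in the four groups yield low adherence by depression status and, by pooling, the crude overall contrast. True, but the article plans confounder adjustment, and the adjusted versions need a model that is not stated.

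**An analysis plan that is not shown may hold more.** It may, so the absence of a mediation method is not itself an error. But the article itself fixes the primary outcome as four groups and the sample size on a different contrast; that mismatch is in the text at hand.

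**The alarming case is extreme.** A reader might infer that the table could show no depression effect at all. That requires full mediation, for example 20% vs 50% low adherence with a 33.3-point effect, hence risks of 1.3% and 34.7% by adherence: a risk ratio of 26 and an odds ratio near 39. The article gives no ground for expecting this.

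**Conclusion.** The point holds as a mismatch between aims, sizing and stated analysis. The article sizes the study on an overall depression contrast because adherence may be an intermediate, then states analyses built on adherence groups. Aim 1 has no stated contrast free of adherence, and the depression–adherence half of aim 2 has no stated model.

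Its size is unknown from the article. Under the assumptions above, 3 of 10 points run through adherence in the worked example and 0–60% over the range; at the lower end nothing is lost. These figures use the planning rates of 18% and 8%, an additive adherence effect equal in both depression groups, and no confounding.

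The four-group analysis remains sound for the joint-risk question, and the 550 patients and 88% power reproduce.

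**What to change.** In the Data analysis section, keep the four-group table for joint risk and add:

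1. A regression of low adherence (MPR below 80%) on baseline depression, adjusted for baseline confounders.
2. A depressed-versus-non-depressed estimate of renal decline not adjusted for adherence, shown with and without HbA1c. HbA1c is in the planned adjustment set but may lie downstream of adherence to hypoglycemic drugs, so adjusting for it could remove part of the effect.

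Optionally, as a secondary exploratory analysis, give direct and indirect effects through adherence on the risk-difference scale with bootstrap intervals. That needs a statement of which MPR period is the mediator: a baseline value that looks back a year precedes the depression measure, and a 12-month value coincides with the outcome. It also needs a sensitivity analysis for unmeasured adherence–outcome confounding.

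One sentence should say whether aim 2 is about joint risk, mediation or both, so that the Study endpoints, Sample-size calculations and Data analysis sections agree.

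Cost: a few lines of text and a little more analysis work. All the variables are already collected, and the sample size does not change.
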